# Laparoscopic versus open distal pancreatectomy (LAPOP): study protocol for a single center, nonblinded, randomized controlled trial

**DOI:** 10.1186/s13063-019-3460-y

**Published:** 2019-06-13

**Keywords:** Minimally invasive, Laparoscopic, Distal pancreatectomy, Pancreatic surgery

## Abstract

**Background:**

Earlier nonrandomized studies have suggested that laparoscopic distal pancreatectomy (LDP) is advantageous compared with open distal pancreatectomy (ODP) regarding hospital stay, blood loss, and recovery. Only one randomized study has been conducted showing reduced time to functional recovery after LDP compared with ODP.

**Methods:**

LAPOP is a prospective randomized, nonblinded, parallel-group, single-center superiority trial. Sixty patients with lesions in the pancreatic body or tail that are found by a multidisciplinary tumor board to need surgical resection will be randomized to receive LDP or ODP. The primary outcome variable is postoperative hospital stay, and secondary outcomes include functional recovery (defined as no need for intravenous medications or fluids and as the ability of an ambulatory patient to perform activities of daily life), perioperative bleeding, complications, need for pain medication, and quality of life comparison.

**Discussion:**

The LAPOP trial will test the hypothesis that LDP reduces postoperative hospital stay compared with ODP.

**Trial registration:**

ISRCTN, 26912858. Registered on 28 September 2015.

**Electronic supplementary material:**

The online version of this article (10.1186/s13063-019-3460-y) contains supplementary material, which is available to authorized users.

## Background

A laparoscopic approach has been introduced for most abdominal procedures over the last 30 years, and a minimally invasive approach for these procedures has become the standard of care [1–5]. The main advantage expected from laparoscopic surgery is decreased patient discomfort and faster recovery, including a shortened postoperative hospital stay. A laparoscopic approach was described for resections of the pancreatic body and tail in the mid-1990s, but the general introduction of this method has been slow [6]. Before the publication of the only available randomized controlled trial comparing laparoscopic distal pancreatectomy (LDP) with open distal pancreatectomy (ODP), some cohort studies and systemic reviews suggested the benefits of the laparoscopic approach [7]. The benefits commonly mentioned are a shortening of hospital stay, reduction in blood loss and complications, and a higher rate of spleen-preserving procedures with LDP [8]. However, selection bias, such as differences in tumor size between the study groups, is commonly found in the available nonrandomized studies [8]. LDP has been in use for over 20 years without a single randomized controlled trial (RCT) supporting its proposed advantages. The LAPOP study was designed and initiated to investigate the hypothesis that a minimally invasive approach would shorten the hospital stay in a cohort of patients undergoing standard distal pancreatectomy [9]. A learning curve was passed and described prior to starting the study [10]. Since the start of the LAPOP study, one RCT using a similar approach has been published, and the results suggest enhanced functional recovery and a shortening of hospital stay using the laparoscopic approach [7].

## Methods

### Design and patients

The LAPOP study is a randomized, controlled, nonblinded, parallel assignment, single-center superiority trial of the effectiveness of LDP versus ODP in the settings of lesions in the pancreatic body or tail, regardless of suspicion of malignancy. Patients who fulfill the inclusion criteria and do not satisfy any of the exclusion criteria will be randomized in a 1:1 manner to LDP or ODP.

All patients with tumors in the body or tail of the pancreas in the South-East health district in Sweden are presented to the multidisciplinary board (MDB) at the study site (Linköping University Hospital), where eligibility screening is performed.

### Sample size

The sample size considerations are based on the primary endpoint hospital stay in an intention-to-treat manner. A one-sided power calculation is used because none of the previous publications indicated an inferiority for LDP. The assumed mean hospital stay is 5 and 7.5 days for LDP and ODP, respectively. The standard deviation is 3.5 with a type I error = 0.05, and 25 patients are needed in each group to achieve a 0.8 power. Thirty patients will be included in each group to include possible drop outs.

### Inclusion and exclusion criteria

The following inclusion criteria are used for the LAPOP study: 1) patients with lesion in the body or tail of the pancreas who require surgery (indication set by multidisciplinary conference); 2) operable patient (based on the local preoperative evaluation); 3) possibility to achieve an R0 resection without resection of additional organs (besides the spleen); 4) patients with a performance status of 0–2 according to the World Health Organization (WHO) scale; 5) written informed consent provided; and 6) age > 18 years.

The following exclusion criteria will be used: 1) pregnancy and/or lactation; 2) patients unable to comply with the protocol because of language or cognitive function; 3) preoperatively defined need to resect organs other than the pancreas and spleen; 4) preoperatively defined division line of the pancreas to the right of the superior mesenteric vein.

### Randomization and inclusion

Randomization will be performed using computer-generated random numbers in blocks of 10 (5:5). A research nurse who will not participate in patient care will perform the randomization. Study group allocation will depend on the contents of sealed opaque envelopes generated in the above-described manner, and envelopes will be opened after patient inclusion. A surgeon in the outpatient clinic will provide written and oral information about the study, and patients who agree to participate will sign a written informed consent.

### Treatment

#### LDP (treatment group)

Patients will receive general anesthesia in a supine position, and four trocars will be placed: one above the umbilicus (12 mm); one in the lateral part of the left rectus abdominis muscle (12 mm); one to the left of the xiphoid process (5 mm); and one in the left flank (5 mm). The surgeon and assisting surgeon (controlling the camera) will stand on the patient’s right side.

The left colonic flexure will be mobilized, and the splenocolic ligament will be divided. Thereafter, the omental bursa will be opened, and the stomach completely mobilized, including the short gastric vessels. The lesion in the pancreas will be identified with or without the help of ultrasonography. The inferior border of the pancreas will be dissected, and a band placed around the pancreas between the lesion and spleen if appropriate. A band will be placed around the pancreas to the right of the lesion (and the splenic vein if splenectomy is intended). Before dividing the pancreas, the splenic artery will be identified and secured using Hem-o-lock clips (Teleflex Medical, [name], Research Triangle Park, NC, USA). In cases of spleen-preserving procedures, the splenic artery will be dissected from the pancreas and left intact. To improve visibility of the superior border of the pancreas, the stomach will be sutured to the anterior abdominal wall. Depending on the preoperative assessment, lymphadenectomy will be performed as indicated for pancreatic adenocarcinoma. The pancreas will be divided using a linear stapler with a cartridge size based on the thickness of the pancreas. A gradual stepwise compression technique and division will be used as described previously to reduce the risk of rupture of the pancreas along the stapling line [11]. Following division of the pancreas, the resection will be performed in a medial to lateral direction. The surgical specimen will be placed in a plastic bag and retrieved through enlargement of the trocar incision above the umbilicus. A 24 CH passive drain will be placed through the trocar incision in the left flank with the tip in front of the pancreatic transection line.

#### ODP (control group)

A midline laparotomy will be performed, retractors placed, and the resection performed essentially as described above. The stomach will be retracted with the retractor instead of sutures, and the splenic artery will be suture ligated instead of using clips. No attempt will be made to dissect around the pancreas between the lesion and the spleen as antegrade resection is applied. The division of the pancreas will be performed in the same manner as the LDP group, and a drain placed in the same manner. Lymphadenectomy will be performed when indicated.

### Conversion to open surgery

Conversion (in the LDP group) is defined as any incision that is not for trocar placement or surgical specimen retrieval. In cases of conversion, analyses will be performed in an intention-to-treat manner.

### Postoperative treatment

Both groups follow a fast-track program that omits the use of a nasogastric tube directly after surgery (in the operating theatre) and encourages oral intake as soon as possible. Epidural anesthesia is allowed in the ODP group but not in the LDP group.

### Study outcomes

The primary outcome variable of the LAPOP study is hospital stay, which is defined as the number of days spent in the hospital after surgery. The study hypothesis is that LDP results in shorter hospital stays than ODP.

Secondary outcomes include functional recovery (key secondary outcome), which is defined as the number of days needed to reach no need for intravenous drug administration or fluids and ambulatory patients who are able to perform activities of daily living (ADL). These outcomes do not exclude discharge with drains or urinary catheters. Other secondary outcomes are perioperative bleeding (assessed by an anesthesia nurse), use of pain medications, complications (according to Clavien Dindo classification), frequency of postoperative pancreatic fistula, quality of life, lymph node harvesting, R0 frequency, and cost.

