### Statistical analysis

Analyses will be based on the intention-to-treat principle. Primary outcome and key secondary outcomes will be tested using *t* tests. Demography, treatment, and clinical data will be reported.

Quality of life will be measured using the EORTC QLQ-C30, EORTC PAN26, and EQ-5D for analyses.

Cost-benefit analysis will be performed for the surgery, postoperative complications, and interventions, days in hospital, need for postoperative outpatient treatment, readmissions for complications, and tumor recurrence. The costs for sick leave will be included.

The study is performed without a data monitoring committee (DMC), and no interim analysis is planned. The adherance to the CONSORT checklist is shown as Additional file 1.

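### The key secondary outcome counts only intravenous treatment, while epidural is allowed in the open arm alone, so recorded recovery can come earlier under ODP and bias the comparison against LDP

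*Protocol article*

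**What the plan says.** All references are to the protocol article.

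- **Study outcomes** names functional recovery as the key secondary outcome and defines it as "the number of days needed to reach no need for intravenous drug administration or fluids and ambulatory patients" capable of daily activities. Three conditions must hold together: no intravenous drugs or fluids, walking, and independence in daily activities.
- **Abstract, Methods** gives the same three: "no need for intravenous medications or fluids and as the ability of an ambulatory patient to perform activities of daily life".
- **Study outcomes** also says which devices are compatible with the outcome: "These outcomes do not exclude discharge with drains or urinary catheters". An epidural catheter is not mentioned.
- **Postoperative treatment** states: "Epidural anesthesia is allowed in the ODP group but not in the LDP group".
- **Statistical analysis** states: "Primary outcome and key secondary outcomes will be tested using *t* tests".

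The definition has no separate condition on pain control or on being managed with oral analgesia.

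**The concern.** The only drug condition in the endpoint is tied to one route, and the protocol itself makes another parenteral route available in one arm only. An ODP patient who walks, manages daily activities and has no drip satisfies the definition even if an epidural is still delivering analgesia. An LDP patient whose analgesia is intravenous at the same point does not. The drug criterion can therefore describe different states in the two arms.

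Randomisation does not remove this, because the difference is imposed by arm. The Discussion treats functional recovery as the main alternative to hospital stay and calls it partly subjective. In a nonblinded trial, an unstated rule leaves each epidural case to the assessor. If stay and functional recovery gave different answers, the scoring of epidurals would be one possible explanation that the published definition could not rule out.

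**Working it through.** **1. The passages side by side.**

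| Patient state (walking, independent, no intravenous fluids) | LDP | ODP |
|---|---|---|
| No intravenous drugs, no epidural | recovered | recovered |
| Intravenous analgesia | not recovered | not recovered |
| No intravenous drugs, epidural running | not allowed under Postoperative treatment | recovered, read literally |

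The arms differ only in the last row. LDP patients can be scored recovered as soon as they meet the three conditions.

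**2. Size of the shift.** Let W be the day on which all the other criteria are met, E the day the epidural stops, and p the share of ODP patients with an epidural. Then

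shift in ODP mean = p × E[max(E − W, 0)].

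The shift is zero for any patient whose epidural stops before the last other criterion is met. The article gives none of W, E or p, so all are assumed here: W gamma with SD 2.5 days, E a fixed day, p from 0.5 to 1.0.

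| Mean of W | E | Under-count per epidural user (days) | Shift in ODP mean, p = 0.5 to 1.0 (days) |
|---|---|---|---|
| 7 | 3 | 0.01 | about 0.01 |
| 6 | 3 | 0.06 | 0.03 to 0.06 |
| 5 | 3 | 0.18 | 0.09 to 0.18 |
| 4 | 3 | 0.47 | 0.23 to 0.47 |
| 4 | 4 | 0.97 | 0.48 to 0.97 |
| 4 | 5 | 1.62 | 0.81 to 1.62 |

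The last row is the least favourable to the plan. It requires about 72% of epidural users to have met every other criterion before a day-5 stop.

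**3. What such shifts would do to the test (illustration only).** The Sample size section powers hospital stay: means 5 and 7.5 days, SD 3.5, one-sided 0.05, power 0.8, 25 per group. This reproduces:

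n = 2 × (1.645 + 0.842)² × 3.5² / 2.5² = 24.2, so 25 per group.

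An exact one-sided t test gives 24.94, also 25, with power 0.80 at 25 and 0.86 at the 30 to be enrolled.

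No difference, SD or power is stated for functional recovery. Borrowing 2.5 days and SD 3.5 from stay, observed difference = 2.5 − shift:

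| Shift (days) | Observed difference | Power, 25 per group | Power, 30 per group |
|---|---|---|---|
| 0 | 2.5 | 0.80 | 0.86 |
| 0.2 | 2.3 | 0.74 | 0.81 |
| 0.5 | 2.0 | 0.64 | 0.71 |
| 1.0 | 1.5 | 0.44 | 0.50 |
| 1.5 | 1.0 | 0.26 | 0.29 |

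Even the largest shift leaves 2.5 − 1.62 = 0.88 days in favour of LDP.

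**The case against.** **Ambulation and daily activities are also required.** This stands. A reader might infer that being off intravenous treatment is enough, or that LDP patients cannot be scored recovered. The definition supports neither.

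**Nothing says that LDP analgesia is intravenous.** This stands too. Both arms follow a fast-track programme with early oral intake, and an LDP patient on oral analgesia is not held back by the drug criterion. Epidural is permitted in ODP, not required. It is therefore not established that recorded ODP recovery does come early; the rule only allows it.

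**The larger figures depend on favourable choices of input.** Agreed. With a planned mean ODP stay of 7.5 days, meeting the other criteria at a mean of day 4 may be optimistic, and later days bring the shift close to zero.

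**The bias is conservative and spares the primary outcome.** Both parts are correct. But a conservative bias is still a bias in the estimate of a superiority comparison. A reader might go further and infer that the result could be reversed. Under the assumptions used here it could not, since 1.62 is less than 2.5 days.

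**The scoring rule may sit in the full protocol or on the hospital-stay form.** Possible, and neither is shown. The point is still not just missing detail: the article fixes the definition, repeats it in the abstract and lists devices that do not count against it. Applied as written, that definition treats the epidural route differently from the intravenous one.

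**Changing a published definition late carries its own risk.** With 53 of 60 patients randomised at submission in a nonblinded trial, a correction made in ODP only, in the direction that favours LDP, would invite criticism. This stands and shapes the fix.

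**Conclusion.** The point holds as a defect in the endpoint definition. Study outcomes and the abstract count only intravenous treatment, Postoperative treatment allows epidural in ODP alone, and nothing in the article reconciles them. The drug criterion can be met earlier in ODP, and any bias runs against LDP.

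Its size cannot be determined from the article. Under the assumptions shown, it ranges from negligible (about 0.1 to 0.2 days or less in the ODP mean) to about 1.6 days in the least favourable case. It is zero wherever the epidural does not outlast the other criteria. The power figures rest on inputs borrowed from hospital stay and contradict no claim in the protocol. The primary outcome is unaffected. The correction is worth making because it is cheap and the size of the bias is unknown.

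**What to change.** Before any outcome comparison, reconcile Study outcomes (and the abstract) with Postoperative treatment:

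- Make the drug criterion: no need for intravenous or epidural drug administration, and no intravenous fluids. Leave the walking and daily-activity conditions as they are.
- Apply it by one rule to all patients in both arms, including any LDP patient who received an epidural, for example after conversion.
- For patients already randomised, take the epidural stop date from existing charts and re-derive the recovery day.
- Report results under both this definition and the published intravenous-only one, and disclose the change and its date.

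If the full protocol or the case report form already states how an epidural is scored, quoting that rule in the outcome definition would settle the ambiguity. A rule that leaves the epidural uncounted would not remove the bias.

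The cost is a few words, one date per epidural user, a retrospective chart check, and a late, disclosed change to a published secondary definition. No change to analgesic care is implied.

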### Follow-up and data collection

Baseline characteristics will be collected using standardized case report forms (CRFs) before randomization. Data for the outcome variables will be collected on separate CRFs for surgical procedure, hospital stay, pathology report, and 90-day follow up. Quality of life will be assessed using the EORTC QLQ-C30 with the addition of the PAN26 module and EQ-5D (Fig. 1).

Study subjects will complete the questionnaires at inclusion, 4–6 weeks after surgery, and 6, 12, and 24 months postoperatively. A research nurse will contact patients who do not return questionnaires to improve follow-up. Survival will be followed up to 24 months postoperatively (Table 1).

**Fig. 1 Fig1:**
[figure not shown]
Trial flow diagram. LDP laparoscopic distal pancreatectomy, OPD open distal pancreatectomy

**Table 1 Tab1:** Schedule of enrollment, interventions, and assessments

	MTB	Outpatient clinic	Surgery	POD1	POD2	POD3	Discharge	4–6 weeks postop	POD90	6 months postop	12 months postop	24 months postop
Screening for eligibility	x											
Informed consent		x										
Randomization		x										
Baseline characteristics		x										
Intraoperative outcomes			x									
Postoperative outcomes				x	x	x	x		x			
QOL assessment		x						x		x	x	x

*MTB* multidisciplinary tumor board, *POD* postoperative day, *postop* postoperatively, *QOL* quality of life

### Statistical analysis

Analyses will be based on the intention-to-treat principle. Primary outcome and key secondary outcomes will be tested using *t* tests. Demography, treatment, and clinical data will be reported.

Quality of life will be measured using the EORTC QLQ-C30, EORTC PAN26, and EQ-5D for analyses.

Cost-benefit analysis will be performed for the surgery, postoperative complications, and interventions, days in hospital, need for postoperative outpatient treatment, readmissions for complications, and tumor recurrence. The costs for sick leave will be included.

The study is performed without a data monitoring committee (DMC), and no interim analysis is planned. The adherance to the CONSORT checklist is shown as Additional file 1.

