## Discussion

Despite its increasing use, LDP has only been compared with ODP in a single randomized trial of 108 patients after a structured nationwide implementation of the method [7, 12]. The results from the LEOPARD trial support the hypothesis that LDP shortens hospital stay, but this finding must be further investigated in different settings to increase the generalizability of the high-level evidence available. Functional recovery may be a more reliable endpoint than hospital stay in multicenter studies, and particularly multinational studies, but it remains partially subjective. Our study is performed in a homogenous population that represents approximately 10% of the Swedish nation. Therefore, differences in routines should not influence the results, and other factors that can influence the length of stay should be equally distributed between the groups due to the randomized nature of the study. Therefore, the more robust endpoint of hospital stay is more suitable as the primary endpoint rather than functional recovery. Due to the structure of the Swedish healthcare system, all patients from the South-east health district (approximately 1 million inhabitants) will be eligible for the study and evaluated at the same tumor board. The study includes all types of tumors in adult patients with no upper limit of tumor size as long as standard distal pancreatectomy may be used. Therefore, the results will be useful for general decision making. The secondary outcomes will provide information on health economic aspects and quality of life.

This study has several limitations that should be acknowledged. Blinding is impractical and will not be used because Swedish patients have access to their health records, including operation notes, and the unit performing the study is small in size. The lack of blinding may be a limitation, but the importance of blinding in surgical studies is largely unknown. The use of fixed size blocks for randomization makes it theoretically possible to know beforehand the allocation of every tenth patient randomized. However, the practical implications of this limitation are minor because of the organization, where the decision to offer participation is made at a multidisciplinary conference based on rigid inclusion and exclusion criteria, and a research nurse informs the patients at the outpatient clinic prior to randomization.

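### The unadjusted t tests are valid, but prespecified adjustment for two or three pre-randomisation covariates would probably add modest precision and correct for chance imbalance

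*Protocol article*

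**What the plan says.** All references are to the protocol article.

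- **Statistical analysis:** "Analyses will be based on the intention-to-treat principle", and "Primary outcome and key secondary outcomes will be tested using *t* tests". The only use stated there for baseline information is that "Demography, treatment, and clinical data will be reported".
- **Design and patients; Randomization and inclusion:** patients "will be randomized in a 1:1 manner to LDP or ODP", in computer-generated blocks of ten. No stratification factor is named.
- **Follow-up and data collection:** "Baseline characteristics will be collected using standardized case report forms (CRFs) before randomization". The variables are not listed.
- **Inclusion and exclusion criteria; Discussion:** WHO performance status 0–2 and any age above 18 are eligible, and "The study includes all types of tumors in adult patients with no upper limit of tumor size".
- **Treatment:** whether lymphadenectomy is done depends on the preoperative assessment, so case mix affects the operation itself.
- **Discussion:** "other factors that can influence the length of stay should be equally distributed between the groups due to the randomized nature of the study".
- **Sample size:** means of 5 and 7.5 days, SD 3.5, one-sided type I error 0.05, power 0.8; 25 per group, raised to 30 for drop-outs.

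**The concern.** Neither the allocation scheme nor the named test takes account of prognostic factors, in a trial of 60 patients whose lesions, fitness and extent of surgery vary. Randomisation balances such factors in expectation, but one sample of 30 per arm can still be uneven. If the uneven factor predicts length of stay, the unadjusted difference carries that imbalance. Variation in stay that baseline factors could explain also stays in the error term, which widens the confidence interval.

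At stake is some precision on the primary outcome and the key secondary outcome, and the ease of interpreting the result if the arms turn out visibly different at baseline.

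**Working it through.** **Inputs.** From Sample size: difference 2.5 days (7.5 − 5), SD 3.5, alpha 0.05, one-sided, 25 then 30 per arm. From Statistical analysis: t test, no covariates. Assumed, because the documents do not give it: R², the share of variance in stay explained by the covariates, taken from 0 to 0.30.

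**1. The plan's own figure.** Normal approximation: n = 2 × (1.645 + 0.842)² × 3.5² / 2.5² = 24.2, rounded up to 25 per arm. The exact one-sided noncentral t calculation also gives 25 (power 0.801). The stated figure therefore reproduces for an unadjusted one-sided t test. At 30 per arm, unadjusted power is 0.862 one-sided and 0.776 two-sided.

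**2. Chance imbalance at 30 per arm.** The SD of the difference in proportions is √(2p(1 − p)/30).

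| Prevalence p | SD | P(difference > 20 points), normal | Same, exact binomial |
|---|---|---|---|
| 0.30 | 0.118 | 0.091 | 0.066 |
| 0.40 | 0.126 | 0.114 | 0.086 |

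These chances are for one factor at a time.

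**3. What an imbalance does to the estimate.** For a continuous covariate that is out of balance by 2 standard errors, the shift in the unadjusted difference is 2 × √R² × 3.5 × √(2/30).

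- R² = 0.10: 2 × 0.316 × 3.5 × 0.258 = 0.57 days.
- R² = 0.30: 2 × 0.548 × 3.5 × 0.258 = 0.99 days.

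The target difference is 2.5 days.

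**4. Power with adjustment, including its cost.** With k covariates, the residual SD is 3.5 × √(1 − R²), the degrees of freedom are 2n − 2 − k, and the variance is inflated by 1 + k/(2n − 3 − k). For k = 3 and n = 30 the inflation is 1 + 3/54 = 1.056. Noncentral t power at 30 per arm:

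| R² | Two-sided | One-sided |
|---|---|---|
| Unadjusted | 0.776 | 0.862 |
| 0 | 0.753 | 0.845 |
| 0.05 | 0.775 | 0.861 |
| 0.10 | 0.796 | 0.877 |
| 0.20 | 0.841 | 0.908 |
| 0.25 | 0.863 | 0.923 |
| 0.30 | 0.885 | 0.937 |

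Break-even with three covariates is at R² of about 0.05. With only 25 evaluable per arm, one-sided power goes from 0.801 unadjusted to 0.777 (R² = 0), 0.814 (0.10) or 0.852 (0.20).

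**5. Validity of the planned test.** In 40,000 simulated null trials with 30 per arm and a covariate of R² = 0.3 left unadjusted, the t test rejected in 0.051 of trials two-sided and 0.048 one-sided, against a nominal 0.05.

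**The case against.** The strongest reply is that nothing here is wrong. Under randomisation the unadjusted t test is valid, its type I error already allows for chance imbalance on average, and it is the analysis for which the trial was sized. All of that stands. It rules out the stronger reading a reader might infer, that the primary test is biased or the result untrustworthy without adjustment.

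Other stronger readings also fail:

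- *The baseline data are thrown away.* The article says such data will be reported. It is accurate only to say that the named test does not use them. An adjusted supportive analysis may also be described in a fuller document that is not shown. The point survives because the article does state the test for these outcomes.
- *Adjustment costs nothing.* Estimating three covariates in 60 patients has a price, and below R² of about 0.05 it is not recovered. No part of the article links any baseline variable to length of stay.
- *Serious imbalance is likely.* At about 7–9% for a factor of 30% prevalence, it is possible but not likely for any single factor.
- *The Discussion claims guaranteed balance.* Its sentence states the ordinary expectation under randomisation, in support of the choice of primary endpoint.
- *The inclusion quality-of-life score is ignored.* The article names no test for quality of life, so its silence cannot be read as a decision.

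**Conclusion.** The point holds as a low-severity suggestion on efficiency. The planned analysis is valid and consistent with the sample size. It gives up some precision if baseline factors predict stay, and it leaves a chance imbalance in case mix uncorrected.

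The size rests on the assumed R². At 0.10–0.25 the gain with three covariates and 30 per arm is about 2 to 9 points of two-sided power (0.776 to 0.796–0.863), or about 1.5 to 6 points one-sided (0.862 to 0.877–0.923). At R² near zero the loss is about 2 points. These figures use the article's SD of 3.5 and difference of 2.5 days, and assume all 30 per arm are analysed.

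**What to change.** Before outcomes are examined by arm, prespecify a linear model of days in hospital on arm plus two or three covariates recorded before randomisation, for example suspected malignancy, age and WHO performance status. First confirm that the chosen variables are on the baseline form, because the article does not list its contents. Use the same model for days to functional recovery. Keep the difference in mean days as the estimate, so that it still answers the question the trial was sized for, and report the unadjusted t test alongside.

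The timing matters: the trial is unblinded, and covariates chosen after seeing results by arm would not be credible. Stratified randomisation is no longer a practical remedy, since Trial status reports 53 of 60 patients already randomised at submission.

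The cost is a sentence or two of analysis text, two or three degrees of freedom, and about 1–2 points of power if the covariates turn out to explain almost nothing.
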